### Recruitment

2.3

We will have 2 cycles of intense recruitment efforts in order to enroll about 20 participants per recruitment cycle. Recruitment approaches include: Flyers placed in clinics and local public venues (eg, libraries, supermarkets); Advertisements in local newspapers; and Online resources (eg, The Miriam Hospital Intranet, Craigslist, and social media).

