### Screening and consent procedures

2.4

Initial contact is made via telephone by interested individuals using a dedicated phone number included in all recruitment materials. Patients signaling interest are then invited for a screening visit.

Full informed consent and HIPAA authorization is obtained in person by the senior research assistant (SRA) after a thorough explanation of the study design, study intervention, and the risks and benefits involved. After informed consent procedures are completed, participants undergo a battery of screening assessments (see Study Assessments for details).

Following the screening visit, patients enter a 2-week run-in period during which they wear accelerometers for the assessment of baseline level of physical activity and obtain clearance for participation from their PCP. Accelerometers are fitted during the screening visit and returned via mail using a prestamped envelope.

Information is collected from all individuals assessed for eligibility (ie, individuals who consented but then resulted noneligible at the completion of the screening process) in order to provide a complete CONSORT diagram and description of the recruitment process. This information will also serve as an indicator of future generalizability of the study.

Once all screening assessments are completed participants are randomly assigned (1:1:1:1 ratio) to the 4 different conditions. The randomization schedule was generated in “R” (cran.us.r-project.org) and is based on a permuted block randomization scheme with small, random-sized blocks. The allocation table was uploaded to an ACCESS database to conceal the sequence and the SRA performs randomization by clicking the “randomize” button.

Participants are not blinded to treatment allocation, but are blinded to the study hypothesis. For practical reasons, the MT instructor cannot be blinded, however s/he is not be involved in data management or analysis. Blinded personnel include the Principal Investigator, co-investigators, and all data entry and analysis personnel.

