### Study interventions

2.5

Participants assigned to Mindfulness Training (MT) alone receive MT based on the curriculum of the manualized Mindfulness-Based Stress Reduction (MBSR) program created by Jon Kabat-Zinn at the University of Massachusetts.^[26]^ Participants attend an orientation session during which they are introduced to the purpose, content, and schedule of the intervention, followed by one two and a half-hour MT sessions once a week for 8 weeks. The MT protocol includes the following basic components of traditional MBSR programs: training in awareness of sensations (“body scan”), a technique based on the cultivation of attention to bodily sensations that normally go unnoticed; training in the awareness of the sensations of breathing; training in directing the attention to simple activities of daily life, and in recognizing when the attention is no longer focused on a specific object of attention; and training in “open awareness”, a practice in which participants are instructed to just notice to which event (physical sensation, sound, visual object, and thought) their attention is spontaneously drawn from moment to moment. The MT instructor is a graduate of the teachers’ training program at the University of Massachusetts Center for Mindfulness with ≥5 years teaching experience.

In addition to MT sessions, participants are instructed to practice mindfulness techniques for 30 minutes daily on their own with the guidance of a digitally recorded, standardized guided mindfulness practice. The recording is provided in different formats (CD or MP3 file) depending on the participant's preference; CD players are offered to participants who do not possess 1 and MP3 versions are uploaded onto the patient's smartphone or other device.

Participants assigned to aerobic training (AT) alone attend a 1-hour AT session 3 times per week for 12 weeks. Sessions consist of a 10-minute warm-up, 40 minutes of aerobic exercise (walking on a treadmill), and 10 minutes of cool down and stretching. Participants receive heart monitors at the beginning of the study and are trained to exercise targeting heart rates at 65% to 75% of the age predicted max heart rate or at an intensity of 12 to 13 in the Borg scale of the rate of perceived exertion. Exercise sessions are supervised by a Master's level (Kinesiology) instructor.

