Participants assigned to the MT + AT condition attend 2 AT sessions and 1 MT session every week for 8 weeks, followed by 3 AT classes per week for 4 additional weeks. Participants are encouraged to participate in as many sessions as possible and are contacted by the SRA each week to remind them of their weekly classes.

Participants assigned to neither intervention continue with the care prescribed by their physicians. To increase retention, at study completion these participants will receive a voucher to attend the YMCA free for 3 months as well as a copy of the MT practice recording.

Although participating in the study, all participants are allowed to continue all medications and treatments (ie, dietary recommendations) prescribed by their care providers. However, participants, regardless of group assignment, are prohibited from engaging in yoga, tai chi, or other mind-body training while enrolled in the study.

To increase overall study retention, patients are asked to provide a home and mobile phone number and email address. The study tracking system identifies participants due for a visit and mail/email reminders or phone messages are then sent to remind patients of their follow-up appointments or class sessions. In addition, we provide a $40 monetary incentive at each of the 3 assessment visits (baseline, 3 month, and 6 month), as well as small gifts such as water bottles and heart monitors. To avoid bias, no incentive is provided to facilitate participation in intervention sessions.

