### Statistical analyses

2.8

Our choice of sample size (n = 40, 10 participants per condition) was determined by the scope and timeline of this project. Given that this is a proof of concept study, our focus is not on strict hypothesis testing but rather on estimates of effect size and corresponding confidence intervals.

Depending upon variable characteristics (categorical or continuous), Fisher exact test or *t* tests will be used to compare participants at baseline on socio-demographic and medical characteristics. Baseline characteristics not balanced by randomization, as well as variables associated with the study outcomes, will be included as covariates in linear or logistic regression analyses.^[58,59]^

Rates of retention and attendance, as well as program satisfaction scores at 3 and 6 months will be calculated separately for each of the 4 groups. The study will be considered feasible if retention rates of at least 80% are achieved, if participants attend at least 70% of the planned sessions, and if they report completion of at least 70% of the assigned individual home practice exercises. For acceptability, each intervention will be considered acceptable if at least 80% of participants indicate grade 4 enjoyment ratings on a visual scale ranging from 0 to 4.

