To determine effect sizes on cognitive function, the ZAVEN^[47]^ composite cognitive score will be calculated for each participant by converting Digital Symbol Substitution Test, F-A-S verbal fluency test, and International Shopping List Test scores to standardized z-scores. The effects of group on ZAVEN scores at 3 and 6 month follow-ups will be estimated using a series of mixed effects longitudinal models controlling for baseline. Models will include a subject-specific intercept to adjust for repeated measures of the outcome over time within participant. A single model will allow for all pairwise comparisons between groups (MT + AT vs MT alone, vs AT alone, vs neither) with the goal of estimating effect sizes and corresponding confidence intervals. A similar approach will be used to assess effects of intervention on each measure of working memory (Groton Maze Learning Test; One-Card Learning Task; and One-Back Test). Last, exploratory mediation analyses will be conducted to assess associations between changes in fitness and other mediators at 3 months with changes in cognitive score at 6 months. As sample size is limited for mediation models, our interest in is estimating effect sizes for both the *a* path (group effects on mediators at 3 months) and *b* path (mediators at 3 months on ZAVEN scores at 6 months), using a similar set of mixed effects models as described previously.

To account for missing data, analyses will be performed according to the intention-to-treat approach.^[60]^ If participants withdraw from the intervention they are asked to complete follow-up assessments. If substantial missing data are encountered, possible options include using accepted statistical methods (eg, use of complete data only, use of multiple imputation, and use of modified weights and model-based procedures). Sensitivity analyses will be conducted using different assumptions regarding the mechanism of missingness.

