### Strengths and limitations

3.1

This is the first study to investigate the effects of AT, MT, and their combination in older adults at risk for dementia. By utilizing a 2 × 2 factorial design, we will be able to describe the role of AT and MT on cognitive function and to determine if the combination may produce effects greater than either intervention alone.

Many prior studies examining the effects of AT and mindfulness-based approaches on cognition, used singular outcome measures such as the Mini-Mental State Examination to describe overall, global cognitive functioning. Although less demanding on researchers and participants, such an approach precludes a more nuanced understanding of the effect on different aspects of cognition. For this study we chose to administer a battery of measures to assess cognitive function across several domains. This comprehensive approach will help explore whether the posited benefits of AT, MT, and MT + AT are domain-specific or extend across domains. Last, this study is also strengthened by rigorous assessments of treatment fidelity throughout delivery of the interventions.

We acknowledge that the interventions proposed in this study are both time and labor-intensive. Participants are asked to contribute between 3 and 4 hours per week over the course of 8 to 12 weeks, not including travel time or time taken to complete study assessments. This schedule was chosen to ensure that participants receive a strong enough “dose” of each intervention and to be as consistent as possible with the structure of the MBSR program.

Detailed feedback will be obtained from participants regarding the length, structure, and quality of all aspects of the MT and AT interventions, and their input will be carefully considered in determining the format of the interventions that will be used in future studies. One possible modification could be to deliver MT using a mobile app instead of requiring participation in class-based sessions, which has the potential to significantly reduce participant burden. Another limitation is the small sample size of this study, as such, results will be only preliminary, and will be used to inform a larger RCT designed to establish the efficacy of this approach.

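### MT is class-based, and AT sessions are also called classes, but the only correlation term named in the mixed models is a subject intercept; if the class ICC is above zero, intervals for contrasts that cross class membership are modestly too narrow

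*Protocol article*

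**What the plan says.** All locations are in the Protocol article.

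- **Analysis model.** Statistical analyses (2.8) estimates group effects on ZAVEN at 3 and 6 months with mixed longitudinal models that control for baseline: "Models will include a subject-specific intercept to adjust for repeated measures of the outcome over time within participant". The working-memory measures and the mediator paths follow a similar approach. The contrasts listed are MT+AT against MT alone, AT alone and neither.
- **Purpose.** The same section puts effect sizes and their confidence intervals ahead of strict hypothesis testing.
- **MT delivery.** Strengths and limitations (3.1) suggests that a later study might "deliver MT using a mobile app instead of requiring participation in class-based sessions", so MT is delivered in classes here.
- **AT delivery.** Study interventions (2.5) has the combined arm going to both kinds of session at first; the later, AT-only part of its schedule is worded "followed by 3 AT classes per week for 4 additional weeks". The section describes AT as treadmill walking and adds: "Exercise sessions are supervised by a Master's level (Kinesiology) instructor".
- **Usual care.** Under 2.5, this arm continues its physicians' care and attends no class.
- **Recruitment and allocation.** Recruitment (2.3): "We will have 2 cycles of intense recruitment efforts in order to enroll about 20 participants per recruitment cycle". Screening and consent procedures (2.4): "participants are randomly assigned (1:1:1:1 ratio) to the 4 different conditions", by permuted blocks of small random size.
- **Size.** Statistical analyses (2.8): "Our choice of sample size (n = 40, 10 participants per condition) was determined by the scope and timeline of this project".

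The article does not give the number or size of classes, whether each recruitment cycle forms its own class, or whether the combined arm sits with the single-intervention arms. It gives no ICC.

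**The concern.** Participants are randomized individually but treated in groups, and only in some arms. This is a partially nested design. People who attend the same MT class share an instructor, a group and a calendar period, so their outcomes may be correlated. Usual-care participants have no such link.

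A subject intercept models correlation between one person's 3-month and 6-month scores. It cannot absorb covariance between different people. Where a class effect lies on one side of a contrast only, or differs between the two sides, its variance enters the estimated difference but not the model's standard error.

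What is at stake is the calibration of the intervals. They are the stated product of the cognitive analysis and are meant to inform a larger trial.

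**Working it through.** **Plan's own figure.** 4 conditions × 10 = 40, and 2 cycles × 20 = 40. The sample size is internally consistent and is not in dispute. It was set by scope, so there is no power calculation to reproduce.

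**Inputs from the article.** 10 per arm; 2 cycles, hence 10 / 2 = about 5 per arm per cycle; usual care unclustered.

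**Assumptions, not in the article.** One class per intervention per cycle; class ICC between 0.01 and 0.10; one follow-up time point as a simplification of the longitudinal model; total variance set to 1 in every arm.

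**Step 1: only MT classes cluster, MT+AT vs neither.** The design effect in the clustered arm is DE = 1 + (5 − 1) × ICC, and in the other arm it is 1. The ratio of true to model SE is √((DE + 1) / 2). Approximate coverage of a nominal 95% interval is 2Φ(1.96 / ratio) − 1.

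| ICC | DE | SE ratio | Coverage |
|---|---|---|---|
| 0.02 | 1.08 | √1.04 = 1.020 | 94.5% |
| 0.05 | 1.20 | √1.10 = 1.049 | 93.8% |
| 0.10 | 1.40 | √1.20 = 1.095 | 92.6% |

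A 4,000-run simulation with t intervals gave 94.0% at 0.05 and 93.1% at 0.10. At ICC 0.01 the ratio is √1.02 = 1.010. The same ratios apply to MT+AT vs AT alone and to MT vs neither, because the MT class effect is again on one side only.

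**Step 2: AT classes cluster too, with the same ICC.** MT+AT now carries two class effects. For MT+AT vs neither the variance inflation is 1 + 4 × ICC, that is 1.20 at 0.05 and 1.40 at 0.10. The model's pooled within-arm variance also falls slightly. With two classes of 5, each class effect lowers an arm's expected sample variance by (1 − 5/9) × ICC = 0.444 × ICC. There are four such effects spread over four arms, so the pooled variance is 1 − 0.444 × ICC.

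- ICC 0.05: √(1.20 / 0.978) = 1.108
- ICC 0.10: √(1.40 / 0.956) = 1.210

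A 40,000-run simulation with t intervals on 36 df agrees:

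| Contrast, classes shared across arms | ICC 0.01 | ICC 0.05 | ICC 0.10 |
|---|---|---|---|
| MT+AT vs neither | 1.02 / 94.5% | 1.11 / 92.3% | 1.21 / 89.7% |
| MT vs neither | 1.01 / 94.8% | 1.06 / 93.7% | 1.12 / 92.1% |
| MT+AT vs AT alone | 1.01 / 94.8% | 1.04 / 94.1% | 1.08 / 93.3% |
| MT+AT vs MT alone | 1.01 / 94.6% | 1.04 / 93.9% | 1.08 / 93.0% |

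Entries are SE ratio / coverage. At ICC 0 the ratio is 1.00 and coverage is 95%.

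**Step 3: dependence on sharing.** When two arms sit in the same class, the common effect cancels in their difference, so the last two rows are small. If each arm had its own classes, MT+AT vs AT alone would rise to 1.15 (91.3%) at 0.05 and 1.29 (87.3%) at 0.10.

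**Step 4: scale.** The half-width that ignores class is 2.028 × √(2/10) = 0.91 SD. For MT+AT vs neither at ICC 0.05 it becomes 0.907 × 1.049 = 0.95 SD with MT clustering alone, and 0.907 × 1.108 = 1.00 SD with both.

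**The case against.** The strongest reply is that the narrowing depends on two things the article does not give, an ICC and a class layout. That stands. A reader might infer that the intervals are certainly too narrow. The documents support this only if the class ICC is above 0, and at 0.01 or below nothing material changes.

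Second, saying that models will include a subject intercept does not say they include nothing else, and an analysis plan that is not shown could add a term. This also stands in part. But the article does state a correlation structure and its purpose, and that structure does not reflect its own delivery format.

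Third, a reader might take AT clustering to be as firm as MT clustering. It is not. It rests on the word classes, applied to supervised treadmill walking with individual heart-rate or exertion targets. The AT figures are therefore a second scenario.

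Fourth, a reader might infer that leaving out recruitment cycle also narrows the intervals. The documents do not support that. With small permuted blocks the arms are nearly balanced within cycle, so a shift common to all arms inflates the residual and costs precision. Nor would a cycle term remove class effects that usual care does not share.

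Finally, the intervals are already wide, results are described as preliminary, and feasibility is the primary question. This limits the importance of the point but does not remove it.

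**Conclusion.** The concern holds in conditional form. The design is partially nested, and the one correlation term named cannot represent similarity between classmates. If the class ICC is positive, intervals for MT+AT vs neither, MT+AT vs AT alone, and single arms vs neither are too narrow. On the assumed layout the shortfall for MT+AT vs neither is about 5% to 10% at ICC 0.05 to 0.10 with MT clustering alone, and about 11% to 21% if AT clusters as well. MT+AT vs MT alone is little affected if those arms share classes.

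The article does not list a pooled comparison of all MT with all non-MT participants, so the point rests on the pairwise contrasts only.

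This is a minor point and a cheap improvement. It bears on the secondary cognitive intervals and leaves the primary feasibility and acceptability criteria unaffected.

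**What to change.** 1. Record each participant's MT and AT class. Report how many classes ran, their sizes, and which arms shared them.
2. Do not rely on a class random effect: about two classes per intervention cannot support an estimated class variance. Instead, report the affected contrasts a second time as a sensitivity analysis, with standard errors computed at assumed class ICCs such as 0.05 and 0.10 and the class sizes that occurred. State the limitation in the text.
3. Separately, include recruitment cycle as a fixed effect in the ZAVEN, working-memory and mediator models. Its purpose is precision; it does not cure class clustering.

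The cost is a few lines of text and code, the logging of class membership, one degree of freedom for cycle, and slightly wider sensitivity intervals.

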### Study design and setting

2.1

This study utilizes a 2 × 2 factorial design. Participants are randomly assigned to MT, AT, both treatments, or neither (see Fig. 1). Study assessments and MT sessions are conducted at the Centers for Behavioral and Preventive Medicine at the Miriam Hospital in Providence, RI, while AT sessions are held at a local YMCA.

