## Discussion

3

Increasing attention is being devoted to preventive strategies to reduce the occurrence of age-related cognitive impairment and dementia. Early observational findings suggested that interventions that improve cognitive skills may be beneficial. Such evidence has spurred a boom in mass-market cognitive “brain training” apps. Although these approaches are becoming increasingly popular, improvements are apparently limited to task-specific domains and do not transfer to other cognitive skills. What has been shown to be effective, instead, is aerobic exercise, with several RCTs documenting the effect of AT on improved cognition in individuals with mild cognitive impairment or dementia.^[18–21]^ Despite the well-established benefit of AT and the promise of cognitive training, only 4 studies examined the combined effects of these 2 approaches in patients with cognitive impairment. Overall, results from these studies suggest that combining AT with cognitive training may be beneficial.^[22–25]^

Parallel to this work, studies have attempted to determine whether mindfulness-based interventions may lead to improvements in cognitive function. MT has shown improvements in cognitive skills (ie, attention, working memory, and executive function) in both healthy younger and older adults.^[28–33]^ To the best of our knowledge though, MT has never been used to improve cognitive function among individuals at risk for dementia. Among mind-body approaches, tai chi, a Chinese martial art combining slow, gentle body movements, and meditative practices, has shown great promise for reducing risk of dementia among older adults,^[61]^ but because tai chi incorporates both physical activity and meditative practices, it is difficult to identify the “active ingredient(s)” responsible for such improvements and it remains unclear whether improvements in cognition are the result of changes in attention and concentration skills from MT, vascular changes from increased physical activity, or a combination of the 2.

In light of this empirical evidence, this pilot study seeks to explore the possible synergistic effects of aerobic exercise and MT on cognitive function. This study is novel in that these interventions will be applied to a clinically relevant population, that is, individuals at risk for developing dementia.

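### The 2 × 2 factorial is analysed only through pairwise group contrasts, which leaves out the AT × MT contrast behind the synergy wording and the more precise averaged AT and MT effects

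*Protocol article*

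**What the plan says.** Section 2.1 of the protocol article states: "This study utilizes a 2 × 2 factorial design". Under section 2.4, "participants are randomly assigned (1:1:1:1 ratio) to the 4 different conditions". Section 2.8 gives the size and its basis: "Our choice of sample size (n = 40, 10 participants per condition) was determined by the scope and timeline of this project". No power calculation is offered, and the same section says that "our focus is not on strict hypothesis testing but rather on estimates of effect size and corresponding confidence intervals".

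For cognition, the model in section 2.8 uses treatment as a single four-level term: "The effects of group on ZAVEN scores at 3 and 6 month follow-ups will be estimated using a series of mixed effects longitudinal models". The contrasts follow: "A single model will allow for all pairwise comparisons between groups (MT + AT vs MT alone, vs AT alone, vs neither". Section 2.7.3 frames the secondary goal the same way, as the effect of group, and expects the combined arm to improve more than either single arm or UC.

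Two later statements describe what the design is for. The Discussion says that "this pilot study seeks to explore the possible synergistic effects of aerobic exercise and MT on cognitive function". Section 3.1 justifies the factorial layout because "we will be able to describe the role of AT and MT on cognitive function", and because it can show whether the combination exceeds either intervention alone.

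The article names no AT effect or MT effect averaged over the other factor, and no AT × MT contrast.

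**The concern.** A 2 × 2 factorial yields two quantities that a plain four-arm comparison does not: the effect of each component averaged over the other, and the interaction, MT+AT − MT − AT + UC. The article invokes the factorial design and mentions synergy, but specifies neither quantity.

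Two things are at stake. First, the combined arm can beat every other arm when the effects are purely additive, so a reader of the pairwise results could credit synergy that was never estimated. Second, the declared product of the cognitive analysis is effect sizes with confidence intervals, meant to inform a larger trial. Interval width is therefore the relevant yardstick, and the averaged effects are more precise than any pairwise contrast from the same 40 participants.

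**Working it through.** **Inputs from the article.** Four cells in a 1:1:1:1 ratio, 10 per cell (sections 2.4 and 2.8). Retention target of at least 80% (section 2.8), used here only as a sensitivity case of 8 per cell. AT alone: 3 sessions a week for 12 weeks. MT + AT: 2 AT sessions a week for 8 weeks, then 3 a week for 4 weeks (section 2.5).

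**Assumptions (not in the article).** Two-sided 95% level, equal residual variance in all cells, one time point, results in residual-SD units. No SD or baseline–outcome correlation is given, so a range is shown.

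**The plan's own figure.** 4 × 10 = 40, which agrees with the stated sample size.

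**Additive example.** Suppose AT and MT each add 0.3 SD and there is no interaction. Relative to UC the cell means are 0, 0.3 (AT), 0.3 (MT) and 0.6 (MT + AT).
- MT + AT minus MT = 0.3
- MT + AT minus AT = 0.3
- MT + AT minus UC = 0.6
- Interaction = 0.6 − 0.3 − 0.3 + 0 = 0

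All three listed contrasts favour the combination, with no synergy.

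**Standard errors, n per cell.** All contrasts come from one model with variance pooled over the four cells, so residual df = 4n − 4.
- Pairwise: √(2/n)
- AT or MT averaged over the other factor (2n vs 2n): √(1/n)
- Interaction: √(4/n)

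**95% half-width = t × SE**

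| Contrast | n = 10, df 36, t = 2.028 | n = 8, df 28, t = 2.048 |
|---|---|---|
| Pairwise | 2.028 × 0.447 = 0.91 | 2.048 × 0.500 = 1.02 |
| Averaged AT or MT effect | 2.028 × 0.316 = 0.64 | 2.048 × 0.354 = 0.72 |
| Interaction | 2.028 × 0.632 = 1.28 | 2.048 × 0.707 = 1.45 |

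The averaged effect is narrower than the pairwise contrast by 1 − 1/√2 = 29%. The interaction is wider by √2 − 1 = 41%.

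**Baseline adjustment.** The model controls for baseline, which multiplies each SE by √(1 − r²) and costs one df. With 10 per cell and an assumed r of 0.5 or 0.7, in units of the unadjusted SD:
- Pairwise: 0.79 or 0.65
- Averaged effect: 0.56 or 0.46
- Interaction: 1.11 or 0.92

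The 29% gain is the same at every r.

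**What the averaged effect means.** Let I be the interaction. Then MT+AT − MT = (AT − UC) + I, so the averaged AT effect is (AT − UC) + I/2. It equals the effect of AT alone only when I is zero.

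**AT schedules.** AT alone: 3 × 12 = 36 sessions. MT + AT: 2 × 8 + 3 × 4 = 28 sessions, or 78% of 36. MT is weekly for 8 weeks in both arms that receive it.

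**The case against.** The strongest reply is that the plan matches its own hypothesis. Sections 2.7.3 and 3.1 ask whether the combination exceeds either intervention alone, and the contrasts listed in section 2.8 answer exactly that. This stands. A reader might infer that the main cognitive question goes unanswered; the text does not support that.

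It can also be said that the roles of AT and MT are covered. Four arms give six pairs. The parenthesis names only the three involving MT + AT, but the sentence speaks of all pairs, which on a fair reading includes AT vs UC and MT vs UC. Those simple effects are a legitimate description of each component. This stands too; what is missing is the averaged version.

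Synergy appears as an aim only in the Discussion, and in exploratory language. The Introduction speaks of a cumulative effect, and the secondary outcomes do not mention synergy. It would be wrong to treat it as a formal objective. The sentence is still a claim about what the study explores, and no planned contrast corresponds to it.

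A reader might also conclude that the plan has chosen the least precise contrasts available, or that the factorial information is lost. Neither is so. The interaction is less precise than any pairwise contrast, and every quantity discussed here is a linear combination of the four group means in the model already planned.

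Finally, treating the trial as four arms is defensible because the AT schedules differ. The averaged AT effect mixes a 36-session and a 28-session programme, and the interaction mixes synergy with that difference. This stands as a real limit on the added contrasts and is a reason to keep the pairwise ones. It does not apply in the same way to the averaged MT effect.

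An analysis plan that is not shown may add contrasts. The article, however, states the model and its contrasts explicitly, and they do not cover everything it says the design will deliver.

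**Conclusion.** The point holds in a limited form. The pairwise analysis is sound for the expectation that MT + AT exceeds each other arm. It cannot separate synergy from additivity, and it leaves unused the averaged effects that would be 29% more precise: about 0.64 against 0.91 SD with complete data, or 0.72 against 1.02 SD at 8 per cell. These figures rest on the 95% level, equal variances and a single time point without gain from baseline adjustment. The ratio depends only on equal cell sizes and equal variances.

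The averaged effects can be read as component effects only if the interaction is small, and this trial cannot establish that: the interaction half-width is about 1.3 to 1.45 SD without gain from baseline adjustment. It would be a mistake to expect 40 participants to settle the synergy question; the interval would mainly show how little is known. The consequence is confined to a secondary, estimation-only aim. The feasibility and acceptability outcomes, which are primary and reported by group, are unaffected.

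**What to change.** Keep the pairwise contrasts in section 2.8, and state that they include AT vs UC and MT vs UC. From the same mixed model, at 3 and 6 months, also report with 95% confidence intervals:

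1. the AT effect averaged over MT and the MT effect averaged over AT;
2. the contrast MT+AT − MT − AT + UC, labelled descriptive, with its expected half-width.

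State that no synergy claim will be drawn from pairwise results. If the interaction is not to be reported, remove the word synergistic from the Discussion.

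Add two caveats: the averaged effects describe the components only if interaction is small; and, because AT totals 36 sessions alone and 28 in MT + AT, the averaged AT effect spans two schedules and the interaction includes that difference.

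The cost is a few contrast statements and two sentences of text. No participants, data or redesign are needed. The downside is more estimates to interpret in a small trial, which the descriptive label addresses.
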